#### 4.3 Stopping Rule:

Throughout the study, we will continually collect data for all applicable participants seen in Nevada's ED regardless of the lower and upper bounds of our planned sample size. We will terminate after we have fulfilled 9 months of follow-up observation for the first enrolled participant.

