#### 4.1 Sample Size:

In 2017, the six participating hospitals reported a total of 308 opioid-related poisoning visits to the ED, representing 37% (308/829) of the total visits statewide. Those numbers are highly conservative, because they are restricted to a small set of ICD-10 billing codes (primary diagnosis of T40.0, T40.1, T40.2, T40.3, T40.4, and T40.6). Other research found that using only ICD-9/10 billing codes related to opioid poisoning results in low sensitivity (as low as 25%). Additionally, rates of opioid-related visits have increased significantly over the past several years in Nevada (+12% 2010-2015, and +22% 2014-2015). Therefore, we anticipate that the actual number of intervention participants will be significantly higher. Using the findings from the sensitivity analysis above, we estimate the possible number of opioid-related poisonings for the 6 intervention hospitals to be 1232. The upper bound of the possible number of participants is represented by the total set of opioid-related ED encounters, which was 2635 in the six intervention hospitals in 2017, representing 37% (2635/7125) of encounters statewide. We anticipate 5% of control patients will access MAT compared to 33% of intervention patients. We anticipate that 7-12% of control patients will experience a non-fatal overdose in the 9 months following their index overdose, and that will be reduced by around 47% among intervention participants. According to unpublished data from the SSA, we anticipate 10% of control participants will die of an overdose in the next year compared to 5% in intervention participants.

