### Measured Variables

- 5 Intervention vs. Standard of Care: The exposure of interest is whether patients receive the MROT program or standard of care. Standard of care will be defined as receiving standard discharge instructions and a passive referral to local services. There are 2 primary outcomes

of interest that will be observed in the 9 months following the patient's initial contact with the MROT: MAT treatment initiation, and non-fatal overdose. Secondary outcomes of interest include MAT treatment retention and fatal overdose. All outcome variables will be measured using data that are available within the SSA databases and which will be provided to the research team in a linked, de-identified data set. Non-fatal overdose will be defined as experiencing an overdose that is treated by ED personnel in the six months subsequent to the initial contact with the MROT. In 2017 Nevada passed AB474, new opioid-related legislation that classified opioid overdose as a reportable condition. This law took effect July 1, 2017 and requires that ED clinicians make a name-based report to the public health authority when they treat an opioid overdose. This mandate should ensure that opioid overdoses are identified in the state surveillance databases. MAT treatment uptake will be measured in three ways. We will obtain records from the SSA that contain information about all patients enrolled in MAT through a state-funded or state-certified provider. First, to measure treatment uptake we will define a dichotomous variable representing whether patients enrolled in a MAT program. Second, we will define "time to treatment" as the time elapsed between the index overdose and enrollment in the MAT program. Third, we will follow MAT patients for 9 months and determine the duration of treatment participation for enrolled patients. Fatal overdose will be defined as a death of a patient that is determined to be opioid related (ICD-10 codes X42, X44, Y12, Y14, T40.0 – T40.6), as reported in the electronic death registry system. We will include all intentional, unintentional, and undetermined deaths in the initial analysis, and will conduct sub-analyses in which only unintentional and undetermined deaths are included.

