## Analysis Plan

- 6 We hypothesize that in the 9 months following their index overdose, patients exposed to the MROT will: H1: be more likely to initiate MAT (Primary outcome) H2: have fewer non-fatal ODs (Primary outcome) H3: be retained in MAT longer (Secondary outcome) H4: be less likely to die of a subsequent OD (Secondary outcome) All analyses will be conducted using the intent-to-treat principle. Demographic and descriptive statistics will be calculated at baseline and at 9-months following the index overdose. The baseline characteristics and main outcomes between the intervention and control groups will be compared using the chi-square test and the two-sample t-test. To test the hypotheses with the dichotomous outcome (initiation of MAT) and the ordinal outcome (incidence of non-fatal OD) we will use generalized linear mixed effects models (SAS PROC GLIMMIX) and Bayesian hierarchical models (SAS PROC MCMC) to account for the complexity of non-normal outcomes and intricate cluster effects due to the interdependence of patients within hospitals. The sensitivity analysis for Bayesian hierarchical models will also be performed. For the time to treatment, retention in treatment, and death due to subsequent OD outcomes, we will apply marginal Cox models (SAS PROC PHREG) to estimate the main effect of intervention exposure and use the robust sandwich covariance matrix estimation approach to account for the intracluster dependence. Individual demographic information including age, race, sex, drug of choice (heroin vs. prescription opioids), insurance type (e.g., Medicaid vs. private), and location of residence (urban vs. rural) will be included in the mixed effects models and marginal Cox models to control for potential confounding effects. We will obtain records from the SSA for 9 months prior to the index overdose for all participants, to allow us to control for prior history of non-fatal overdose and MAT utilization. Other covariates at the hospital level will include location (e.g., Northern Nevada vs. Southern Nevada, rural vs. urban) and hospital type (e.g., regional, university, trauma center, etc.). In addition to the statistical approach described above, we will also employ a propensity score (PS) matching approach as a secondary analysis. PS matching is particularly well-suited to "natural experiments" in which assignment to condition cannot be manipulated, such as the implementation of state programs. The approach involves calculating the probability of assignment to a treatment or exposure using logistic regression in which we enter observed characteristics that could influence assignment. In this case, known characteristics of patients such as age, sex, location of residence (rural vs. urban), previous history of overdose, or previous history of MAT enrollment. The PS reduces the large set of possible covariates that could influence selection into the intervention or control

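### The stopping rule ends the study when the first enrolled participant reaches 9 months, which contradicts the 9-month per-patient window of the hypotheses and primary outcomes

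*Protocol*

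**What the plan says.** Section 4.3 (Stopping Rule) has two sentences. The first sets open-ended collection: "we will continually collect data for all applicable participants seen in Nevada's ED regardless of the lower and upper bounds of our planned sample size". The second sets the end: "We will terminate after we have fulfilled 9 months of follow-up observation for the first enrolled participant". No enrolment closing date is given, and nothing extends follow-up or record extraction past that point.

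Elsewhere the window is 9 months for each patient:

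- Analysis Plan (and likewise Hypotheses), introducing all four hypotheses: "We hypothesize that in the 9 months following their index overdose, patients exposed to the MROT will" show the stated benefits.
- Measured Variables, on the two primary endpoints: "of interest that will be observed in the 9 months following the patient's initial contact with the MROT: MAT treatment initiation, and non-fatal overdose".
- Measured Variables, on retention: "Third, we will follow MAT patients for 9 months and determine the duration of treatment participation for enrolled patients".
- Analysis Plan, on descriptive summaries: "Demographic and descriptive statistics will be calculated at baseline and at 9-months following the index overdose".

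One sentence in Measured Variables differs. It defines non-fatal overdose as an "overdose that is treated by ED personnel in the six months subsequent to the initial contact with the MROT".

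The Analysis Plan models MAT initiation as dichotomous and non-fatal overdose as ordinal, using generalized linear mixed models and Bayesian hierarchical models. Marginal Cox models are used for time to treatment, retention and overdose death.

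**The concern.** When patients enter continually and collection ends 9 months after the first one enters, every later patient has less than 9 months on record. The stopping rule and the outcome windows therefore cannot both be followed.

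The rule matters because it is the only statement in the protocol that fixes the end of data collection, and so the end date of the state extract. An analysis plan could adjust for unequal follow-up, but it could not recover events that fall after the extract closes. The two primary outcomes are the most exposed. They are analysed as a yes/no and an ordinal result, with no stated allowance for unequal follow-up, so they would not estimate the 9-month rates on which section 4.1 is built.

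**Working it through.** **Nearest figure in the plan.** The stopping rule has no derived figure of its own. The closest is the power in section 4.2: at least 82% for effect size 0.2 with 308 + 521 patients. Two-sided at 0.05, 0.2 × √(308×521/829) = 2.78, and Φ(2.78 − 1.96) = 79.5%. An equal split of 829 gives 82.1%. This small gap is a separate matter and does not depend on the stopping rule.

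**Inputs from the protocol.**

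- Annual volume, conservative (4.1): "In 2017, the six participating hospitals reported a total of 308 opioid-related poisoning visits to the ED", out of 829 statewide, hence 308 + 521.
- Annual volume, anticipated (4.1 and 4.2): 1232 + 2084 = 3316, which is the 2017 count divided by a sensitivity of 25% (308/0.25 = 1232; 521/0.25 = 2084).
- Control non-fatal overdose of 7-12% in 9 months, reduced by about 47% (4.1). Intervention rates are then 0.53 × 7% = 3.71% and 0.53 × 12% = 6.36%.
- MAT access of 5% against 33% (4.1).
- Two-sided alpha of 0.05.

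**Assumptions, not in the protocol.** Even accrual, constant hazard, independent patients, 2017 visits counted as patients (as section 4.2 does), and the MAT rates read as 9-month rates.

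**Step 1: follow-up under the literal rule.** A patient entering at month u has 9 − u months. With u uniform on 0 to 9, the mean is 4.5 months. The share reaching six months is (9 − 6)/9 = one third. Those entering on the first day are about 0.4% of the total (829/365 = 2.3 of 622).

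**Step 2: accrual by the end.** Nine twelfths of a year gives 308 × 0.75 = 231 and 521 × 0.75 = 391 at the conservative volume. At the anticipated volume it gives 924 and 1563.

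**Step 3: expected observed event rates.** With hazard λ = −ln(1 − p)/9, the average event probability is 1 − (1 − e^(−9λ))/(9λ), which equals 1 − p/(−ln(1 − p)).

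| 9-month rate p | Observed under the rule |
|---|---|
| Control overdose 7% | 1 − 0.07/0.07257 = 3.5% |
| Control overdose 12% | 1 − 0.12/0.12783 = 6.1% |
| Intervention overdose 3.71% | 1 − 0.0371/0.03781 = 1.9% |
| Intervention overdose 6.36% | 1 − 0.0636/0.06571 = 3.2% |
| MAT, control 5% | 1 − 0.05/0.05129 = 2.5% |
| MAT, intervention 33% | 1 − 0.33/0.40048 = 17.6% |

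**Step 4: power for non-fatal overdose.** Cohen's h = 2·arcsin√p₁ − 2·arcsin√p₂, and power ≈ Φ(h·√(n₁n₂/(n₁+n₂)) − 1.96). With complete follow-up h is 0.148 (7% control rate) or 0.198 (12%). Truncated, it is 0.105 or 0.140.

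| Patients (intervention + control) | √(n₁n₂/(n₁+n₂)) | Follow-up | Power, 7% to 12% control rate |
|---|---|---|---|
| 308 + 521 | 13.91 | full 9 months | 54-78% |
| 308 + 521 | 13.91 | truncated | 31-49% |
| 231 + 391 | 12.05 | truncated (literal rule) | 24-39% |
| 1232 + 2084 | 27.83 | full 9 months | 98-99.9% |
| 924 + 1563 | 24.10 | truncated (literal rule) | 71-92% |

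The second row shows that lost follow-up, rather than shorter accrual, accounts for most of the fall. A pooled two-proportion formula gives 50-76% falling to 21-35% at the conservative volume, so the result does not depend on the choice of formula.

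**Step 5: MAT initiation.** At 2.5% against 17.6% with 231 + 391 patients, power stays above 99%.

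**The case against.** The strongest reply is that this is a wording error. Every other section sets 9 months per patient, so the rule most simply contains a slip for the last participant, or uses termination to mean closing enrolment. That is quite possible, but the protocol states neither, and it remains the only rule that fixes the end of data collection. The point is therefore a contradiction to reconcile, not proof that the sponsor intends truncated follow-up.

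Several stronger conclusions might be inferred and are not supported:

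- **That all the 9-month outcomes become inestimable.** The Cox models for time to treatment, retention and overdose death can use censored follow-up, though with little information late in the window.
- **That truncated patients are counted as non-events.** The protocol does not say this. It only states no allowance for unequal follow-up in the primary models, and an analysis plan that is not shown may add one.
- **That the study misses its planned size.** This holds only against the floor of 829. At the anticipated volume, nine months gives 924 + 1563 = 2487, about three times the 829 that section 4.2 calls sufficient, and section 4.3 says collection is not bound by the planned sizes.
- **That the comparison is biased.** This needs the arms to accrue on different calendars. Roll-out dependent on hospital uptake (Design Plan) makes it possible, but six hospitals are expected to be implementing at the start, and no difference is shown.

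The six-month definition of non-fatal overdose softens the problem without removing it. Under even accrual about two thirds of patients would still lack a full six months. Also, the 54-78% starting power at the floor volume is already below 80%, which the stopping rule did not cause.

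**Conclusion.** The point stands as an internal contradiction that should be corrected before the data extract is fixed. Section 4.3 as written cannot be reconciled with the 9-month windows in Hypotheses, Measured Variables and Analysis Plan, and Measured Variables itself gives two windows for non-fatal overdose.

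That nearly all patients would fall short of 9 months follows from the text under any accrual not concentrated in the first days. The size of the effect on rates and power rests on the assumptions listed in the working. The effect is large for non-fatal overdose at the conservative volume and moderate at the anticipated volume. For MAT initiation power is not threatened, but the quantity estimated would no longer be a 9-month rate.

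**What to change.** Replace the second sentence of section 4.3 with a rule that does three things: states an enrolment closing date; ends data collection when the last enrolled participant has completed 9 months from the index ED visit, or has died; and requests the state extract through that date. In the same amendment, reconcile the six-month and 9-month windows for non-fatal overdose in Measured Variables.

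Every participant can then have the full window. With 12 months of accrual, for example (an assumption), data collection would run about 12 + 9 = 21 months. The data are de-identified state records, so the change needs a short amendment and a later extract, with no extra patients or procedures. The downside is longer calendar time to the final data.

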### Measured Variables

- 5 Intervention vs. Standard of Care: The exposure of interest is whether patients receive the MROT program or standard of care. Standard of care will be defined as receiving standard discharge instructions and a passive referral to local services. There are 2 primary outcomes

of interest that will be observed in the 9 months following the patient's initial contact with the MROT: MAT treatment initiation, and non-fatal overdose. Secondary outcomes of interest include MAT treatment retention and fatal overdose. All outcome variables will be measured using data that are available within the SSA databases and which will be provided to the research team in a linked, de-identified data set. Non-fatal overdose will be defined as experiencing an overdose that is treated by ED personnel in the six months subsequent to the initial contact with the MROT. In 2017 Nevada passed AB474, new opioid-related legislation that classified opioid overdose as a reportable condition. This law took effect July 1, 2017 and requires that ED clinicians make a name-based report to the public health authority when they treat an opioid overdose. This mandate should ensure that opioid overdoses are identified in the state surveillance databases. MAT treatment uptake will be measured in three ways. We will obtain records from the SSA that contain information about all patients enrolled in MAT through a state-funded or state-certified provider. First, to measure treatment uptake we will define a dichotomous variable representing whether patients enrolled in a MAT program. Second, we will define "time to treatment" as the time elapsed between the index overdose and enrollment in the MAT program. Third, we will follow MAT patients for 9 months and determine the duration of treatment participation for enrolled patients. Fatal overdose will be defined as a death of a patient that is determined to be opioid related (ICD-10 codes X42, X44, Y12, Y14, T40.0 – T40.6), as reported in the electronic death registry system. We will include all intentional, unintentional, and undetermined deaths in the initial analysis, and will conduct sub-analyses in which only unintentional and undetermined deaths are included.

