## Description

The over-arching goal of this research is to test the effectiveness of a Mobile Recovery

- 1 Outreach Team (MROT) intervention for opioid overdose and/or opioid use disorder patients treated in Nevada's Emergency Departments (EDs). MROT's will provide peer coaching and mentorship, referrals to medication-assisted treatment (MAT), and opioid overdose education and naloxone as part of the State's SAMHSA STR Program. We will accomplish the research goal through the following two aims: (1) Determine the effectiveness of the MROT on (a) subsequent overdose, and (b) MAT uptake among patients presenting to a hospital ED for opioid overdose, and (2) Evaluate the MROT implementation and fidelity through comprehensive process evaluation. In addition, the research will examine the feasibility and acceptability of a mobile team intervention model in rural Nevada. Because we know Nevada has a unique landscape with many cities located in rural/frontier areas where a traditional model may not be feasible, we will expand our feasibility/acceptability research and outcomes evaluation to include examining the impact of alternative models in hospitals in the rural/frontier regions of Nevada.

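### The non-fatal overdose hypothesis claims fewer overdoses, but the outcome counts only ED-treated ones, and the intervention itself can change whether an overdose reaches an ED

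*Protocol*

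**What the plan says.** Section 5 (Measured Variables) defines the outcome: "Non-fatal overdose will be defined as experiencing an overdose that is treated by ED personnel". It adds that "All outcome variables will be measured using data that are available within the SSA databases", so there is no second source for this endpoint.

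The hypothesis carries no such limit. Section 6 (Analysis Plan) has "H2: have fewer non-fatal ODs (Primary outcome"; section 2 (Hypotheses) states the same comparison as H3.

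The arms differ in what they are given. Section 1 (Description): "MROT's will provide peer coaching and mentorship, referrals to medication-assisted treatment (MAT), and opioid overdose education and naloxone". Section 5, for controls: "Standard of care will be defined as receiving standard discharge instructions and a passive referral to local services".

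On completeness, section 5 relies on AB474, which "requires that ED clinicians make a name-based report to the public health authority when they treat an opioid overdose", and concludes: "This mandate should ensure that opioid overdoses are identified in the state surveillance databases".

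**The concern.** The recorded outcome is the product of two things: whether a survived overdose occurs, and whether it is treated in an ED. The hypothesis concerns only the first, but naloxone and overdose education can act on the second. A survived overdose reversed at home and never brought to an ED is scored as no overdose, and as the arms are described, that route is made easier in one of them.

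The reverse is also possible. Education may lead more people to seek care, and naloxone may turn would-be deaths into survived overdoses. Both would raise the recorded count under MROT. Either way, a difference between arms in the recorded outcome cannot be read directly as a difference in overdoses, and this is one of the two primary outcomes.

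**Working it through.** **1. Does anything in the protocol repair this?**

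- *AB474.* The duty begins when an ED clinician treats the overdose. It can improve capture among ED-treated cases and adds nothing outside the ED.
- *Covariates and propensity matching (section 6).* These use patient and hospital characteristics and prior history. Whether a later overdose reaches an ED is decided after exposure, so balancing the arms at baseline does not remove the difference.
- *Patient interviews (section 4, Sampling Plan).* They follow contact with the outreach team, so they offer no control comparison.
- *Fatal overdose.* It comes from the death registry and does not depend on ED treatment, but it is a secondary outcome and does not measure survived overdoses.
- *Sensitivity analysis.* The only one named for this outcome concerns the Bayesian models.

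**2. How large could the effect be?** The protocol states no figure for this, so there is none to reproduce. The following is an illustration.

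Inputs from the protocol: control risk p = 7% to 12% over nine months (section 4.1); 308 vs 521 and 1232 vs 2084 intervention vs control patients (section 4.2); two-sided 0.05 (sections 4.2 and 6.1).

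Assumption, not in the documents: a net share f of intervention-arm overdoses that would have been ED-treated is not. A negative f means more reach an ED. With no true effect, the recorded intervention risk is q = p(1 − f).

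Chance of a significant result in the direction of the bias, by the two-proportion z-test with independent patients:

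Φ[(|p − q| − 1.96·s0) / s1], where

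- s0 = √[p̄(1 − p̄)(1/n_c + 1/n_i)], with p̄ the pooled risk,
- s1 = √[p(1 − p)/n_c + q(1 − q)/n_i].

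Worked case, p = 12%, f = 20%, 1232 vs 2084:

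- q = 0.12 × 0.8 = 0.096 and |p − q| = 0.024
- p̄ = (2084 × 0.12 + 1232 × 0.096)/3316 = 0.1111
- s0 = 0.01129, s1 = 0.01101
- (0.024 − 1.96 × 0.01129)/0.01101 = 0.17, so Φ = 56.7%

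Worked case, same sample and p, f = −20%:

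- q = 0.12 × 1.2 = 0.144 and |p − q| = 0.024
- p̄ = 0.1289, s0 = 0.01204, s1 = 0.01228
- (0.024 − 1.96 × 0.01204)/0.01228 = 0.03, so Φ = 51.3%

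| Net f | Recorded q (p = 7% / 12%) | Apparent effect | 308 vs 521 | 1232 vs 2084 |
|---|---|---|---|---|
| 0 | 7% / 12% | none | 2.5% / 2.5% in each direction | 2.5% / 2.5% in each direction |
| 10% | 6.3% / 10.8% | benefit | 5.6% / 7.3% | 11.5% / 17.7% |
| 20% | 5.6% / 9.6% | benefit | 11.5% / 17.9% | 34.9% / 56.7% |
| −20% | 8.4% / 14.4% | harm | 11.6% / 17.2% | 31.8% / 51.3% |

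**3. What moves these figures.** An analysis that accounts for clustering within hospitals, as section 6 plans, would have larger standard errors and lower rejection rates. The risks used are for nine months. The sentence in section 5 that defines the outcome goes on to a six-month window, although the protocol elsewhere states nine months; a lower six-month risk would also lower the rates.

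**The case against.** The measure is stated openly, and ED-treated overdose is a legitimate, practical endpoint for linked state data. That stands: the fault lies in the label and the claim, not in choosing the endpoint. The AB474 sentence directly follows one about ED clinicians and can be read as limited to the cases they treat. That reading is fair, but the words as written are wider.

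The missing sensitivity analysis is not itself a fault, because the SAP is not shown and such an analysis commonly belongs there. What this protocol fixes is the definition, the hypothesis and the AB474 sentence.

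Three stronger readings are tempting, and the documents support none of them.

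- *That the bias favours MROT.* A reader might infer this because naloxone is the obvious route. Help-seeking and averted deaths push the other way, and no document gives the balance.
- *That the anticipated 47% reduction is an artefact.* A net f of 47% would reproduce it arithmetically (12% × 0.53 = 6.4%), but nothing makes that value likely. The protocol does not say how many patients would receive or use naloxone, how many reversals bypass the ED, or that controls have no naloxone from elsewhere.
- *That a claim of fewer overdoses should be allowed only if it survives a range of f.* No plausible range can be drawn from the documents. At f = 0.5, a wholly real 47% reduction becomes 0.53/0.5 = 1.06, so the protocol's own target would fail by construction.

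**Conclusion.** The point holds as a mismatch between hypothesis and measurement. The hypothesis is about overdoses, the outcome is about ED-treated overdoses, and the intervention can alter the link between the two in one arm. A significant result would support a statement about ED-treated overdose, not about overdose as such.

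How much this matters in practice cannot be determined from the protocol. The illustration shows only that a modest net shift of 20% in either direction, if it occurred, would raise the chance of a misleading significant result from 2.5% to between about 12% and 57%, depending on sample, risk and direction. Those figures rest on an assumed f, independent patients and nine-month risks, and should not be quoted as the trial's error rate. A larger sample does not reduce the bias; it makes a biased difference more likely to reach significance.

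**What to change.** 1. In sections 2, 5 and 6, name the outcome and its hypothesis (H3 in section 2, H2 in section 6) *ED-treated non-fatal overdose*, and limit the conclusion to that.
2. Limit the AB474 sentence in section 5 to overdoses treated in an ED.
3. Add a descriptive tipping-point analysis from the planned clustered model. Express the effect as a ratio of risks or counts (section 6 calls the outcome ordinal, and the scaling does not apply to an odds ratio), divide it by (1 − f), and report the net f at which the 95% CI first includes no effect. With limits L and U, this is f = 1 − U if the interval lies below 1, and f = 1 − L, a negative value, if it lies above 1. Present it for both directions and attach no pass/fail rule.
4. Reconcile the six-month window in section 5 with the nine months stated elsewhere.

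The cost is protocol wording and one extra analysis on data already to be obtained. The downside is a narrower claim for this hypothesis.

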## Design Plan

- 3 Data is collected from study subjects that are not randomly assigned to a treatment. This includes surveys, "natural experiments," and regression discontinuity designs.

We will employ a quasi-experimental design to test the effectiveness of the MROT. Given the logistical and political considerations of evaluating the real-world implementation and effectiveness of a SAMHSA-funded program, a randomized controlled trial (RCT) is infeasible. Because this study is explicitly linked to, but not in total control over, the rollout of the SAMHSA-funded intervention, the study design must accommodate the fact that the SSA will implement a highly complex set of activities and is dependent on uptake of the program by each hospital ED. This logistical constraint makes it impossible to randomize en bloc. Therefore, a quasi-experimental design that rigorously controls for sources of confounding and bias is preferable. We anticipate there will be six hospital EDs in the implementation phase at the beginning of the study. Patients from these six hospitals who present with opioid overdose or a primary or secondary diagnosis of Opioid Use Disorder (OUD) and have contact with the MROT will be the intervention participants. Patients who present with these conditions at the hospitals that have not yet adopted the MROT program will serve as the control participants. We will analyze the data using a traditional approach that controls for sources of confounding and bias, while adjusting for clustering within hospitals. Also, we will analyze the data using a Propensity Score Matching approach to mitigate bias and support our ability to make causal inferences. All patient data will be obtained as de-identified secondary data from our state partners.

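### The primary non-fatal overdose outcome has two window lengths (six and nine months) and two time origins, and neither origin exists for every patient

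*Protocol*

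**What the plan says.** **Window.** Section 5 (Measured Variables) introduces the two primary outcomes as "of interest that will be observed in the 9 months following the patient's initial contact with the MROT: MAT treatment initiation, and non-fatal overdose". Later in the same section, the only operational definition of non-fatal overdose is "an overdose that is treated by ED personnel in the six months subsequent to the initial contact with the MROT".

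**Time origin.** Section 5 counts from MROT contact. The Analysis Plan (Section 6) opens with "We hypothesize that in the 9 months following their index overdose, patients exposed to the MROT will", and Section 2 (Hypotheses) has the same statement. The planning rate in Section 4.1 is also counted from the index overdose: "7-12% of control patients will experience a non-fatal overdose in the 9 months following their index overdose". Within Section 5, time to treatment runs from the index overdose too, and the look-back for prior history in Section 6 ends there.

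**Who is in the groups.** Section 3 (Design Plan) makes MROT contact part of the definition of an intervention participant and takes controls from hospitals that have not yet adopted the program. Eligibility is wider than overdose, because it covers patients "who present with opioid overdose or a primary or secondary diagnosis of Opioid Use Disorder (OUD".

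**End of study.** Section 4.3 ends the study once the first enrolled participant has nine months of follow-up.

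**The concern.** A primary outcome needs one start date and one length, both available for every patient analysed. This one has two lengths inside a single section. It also has two start dates: the first does not exist for controls, and the second may not exist for patients who qualify through an OUD diagnosis alone. An analyst has to override some sentence of the protocol to compute the outcome at all.

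The study is non-randomised and uses existing state records, so the choice could be made after outcomes are visible, and it could be made differently in the two groups. A difference in window length between groups would produce an apparent effect where there is none. A shorter window used in both groups would cost events and power on an outcome that is already uncommon.

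**Working it through.** **1. The passages side by side**

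| Protocol section | Length | Start |
|---|---|---|
| 2 Hypotheses | 9 months | index overdose |
| 4.1 Sample Size (planning rate) | 9 months | index overdose |
| 5 Measured Variables, introduction of primary outcomes | 9 months | initial MROT contact |
| 5 Measured Variables, definition of non-fatal overdose | 6 months | initial MROT contact |
| 6 Analysis Plan | 9 months | index overdose |

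No section says which entry prevails. Contact is missing for controls by the group definitions in Section 3. The index overdose may be missing for patients enrolled on an OUD diagnosis.

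**2. Inputs for the size of the problem.** From Section 4.1: control risk 7–12% over nine months, and an expected effect "that will be reduced by around 47% among intervention participants". From Section 4.2: 308 vs 521 patients (N=829) and 1232 vs 2084 (N=3316), alpha 0.05. From Section 6.1: two-sided tests. Added assumptions, not in the protocol: constant hazard, a binary outcome and independent patients.

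**3. The plan's own power figure.** Section 4.2 states at least 82% power for a generic effect size of 0.2 at N=829. It is not tied to any outcome or window. At 308/521 a two-sided comparison with a standardised difference of 0.2 gives 79.5%; an equal split of 829 gives 82.1%. That gap is a separate matter and does not affect this point.

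**4. Six-month risks.** p6 = 1 − (1 − p9)^(6/9).
- Control: 7% → 1 − 0.93^(2/3) = 4.7%; 12% → 1 − 0.88^(2/3) = 8.2%.
- Intervention at nine months: 0.53 × 7% = 3.71%; 0.53 × 12% = 6.36%. At six months: 2.5% and 4.3%.
- Share of control events lost: 1 − 4.72/7 = 33%; 1 − 8.17/12 = 32%.
- Ratio of intervention to control risk at six months: 2.49/4.72 = 0.527 and 4.29/8.17 = 0.525, against 0.53 at nine months. A six-month window used in *both* groups leaves the ratio essentially unchanged.

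**5. Different windows by group, no true effect.** Six months for MROT patients against nine for controls gives p6/p9 = 4.72/7 = 0.67 and 8.17/12 = 0.68. This is a spurious reduction of about 32–33%, against a hypothesised 47%.

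**6. Power with a common window.** Cohen's h = |2·arcsin√pC − 2·arcsin√pI|; z = h·√(n1·n2/(n1+n2)); power = Φ(z − 1.96). The multiplier is √(308×521/829) = 13.91 at N=829 and √(1232×2084/3316) = 27.83 at N=3316.

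| Window | Control vs intervention | h | Power, N=829 | Power, N=3316 |
|---|---|---|---|---|
| 9 months | 7% vs 3.71% | 0.148 | 54% | 98% |
| 9 months | 12% vs 6.36% | 0.198 | 78% | >99% |
| 6 months | 4.7% vs 2.5% | 0.121 | 39% | 92% |
| 6 months | 8.2% vs 4.3% | 0.163 | 62% | 99% |

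A two-proportion test, with the 47% reduction applied directly to the six-month control rate, gives 50–76% falling to 35–57% at N=829, and 98% or more falling to 91–99% at N=3316. The pattern is the same.

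**The case against.** Part of the opposing case stands. Most of the protocol says nine months, and the six-month sentence may be a slip. The abstract describes peer specialists seeing patients in the ED, so contact and the index visit may usually fall together in the intervention group, and the anchor conflict may be loose wording for most patients. The power loss is material only at N=829, which Section 4.2 calls very conservative; at the size it reasonably anticipates, power stays at 92% or more. Events concentrated soon after the index visit would make the loss smaller than constant hazard implies. Section 6 also calls the outcome ordinal, so a binary calculation is an approximation. None of this gives controls a contact date or says which window applies.

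A reader might infer that anchoring on MROT contact builds in immortal-time bias in favour of the intervention. The documents do not support that. Follow-up that starts at contact leaves out the time before contact, so that time is not credited to the MROT group as event-free. The protocol does not document contact at a later visit. If it did occur, that visit could itself be a treated overdose, so the gap is not guaranteed free of non-fatal events and the direction of bias is not determined. Immortal time would arise if follow-up started at a first visit while exposure was set by a later contact, which any correction must avoid.

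A reader might also take the risk ratio of 0.68 as what the study will produce. It is the consequence of one reading that the text leaves open; nothing says that the team intends different windows by group.

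**Conclusion.** The point holds as a contradiction in the definition of a primary outcome, and it should be corrected before analysis. The textual finding needs no assumption: the window is six or nine months, the origin is MROT contact or index overdose, and neither origin covers all patients described in Section 3. This is not detail left to a statistical analysis plan, because any such plan would have to contradict some sentence of the protocol.

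Validity matters more than power here. Unequal windows by group could by themselves create an apparent reduction of about a third. A common six-month window would leave the ratio intact but cost 15 to 16 percentage points of power at N=829 (54 to 39, and 78 to 62), and at most about 6 points at N=3316 (98 to 92). These sizes rest on constant hazard, a binary outcome and independent patients; clustering within hospitals is ignored. No claim is made about the direction of any bias from the anchor alone.

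**What to change.** State one rule for both groups and all outcomes: time zero is the date of the index qualifying ED visit, the window is nine months (the length used everywhere except one sentence), and the index event itself does not count as an outcome.

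- In Section 5, replace the six-month window and the MROT-contact origin.
- In Sections 2, 4.1, 5 and 6, replace the index overdose as origin with the index ED visit, so that OUD-only patients have a start date for outcomes, time to treatment and look-back.
- Assign exposure at that same visit, so that a later MROT contact does not reclassify a patient. This fits the intent-to-treat principle stated in Section 6, and the definition of intervention participants in Section 3 should be worded to match.
- Reconcile Section 4.3. Read literally, a patient enrolled k months after the first has only 9 − k months of follow-up. Either extend observation so that every patient can complete nine months, or state how incomplete follow-up is censored for each outcome.

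A covariate for index type (overdose or OUD without overdose) is optional and not needed to resolve the contradiction.

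Cost: the window and origin are wording changes, provided the linked hospital file carries the visit date for every patient, as should be expected. The exposure rule needs a decision, and the stopping rule may need either longer data collection or an explicit censoring rule.
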